### Digital marker selection and validation

2.3

The Expert Panel reviewed potential early diagnostic markers of PD with the aim of creating a set of digital markers suitable for large volume screening of the general population and which could be delivered using the digital platform (Figure 4).

**Figure 4 fig4:**
[figure not shown]
Application interface of the digital assessment package and how the assessment was undertaken.

#### Digital marker selection

2.3.1

Digital markers identified for inclusion in the Parkinson’s disease risk survey were selected following a review of published studies that have used mobile devices and machine learning tools to quantify PD (83–85, 87). These studies have shown that using a combination of tests with machine learning-based analysis it is possible to distinguish subjects with PD from controls with a high degree of sensitivity and specificity. Common testing activities for PD diagnosis using smartphone applications include gait, voice, finger tapping, memory tests and questionnaires. For objective testing of motor function, the Parkinson’s disease risk survey will use a smartphone application to collect data on spoken voice, tremor, dexterity, and mobility. All selected markers are ones that ChulaPD has considerable research experience with. The final digital marker selection includes eight variables, as described in Table 4: voice vowel, voice sentences, resting and postural tremor, alternate finger tapping, “pinch-to-size” test, and gait and balance tests. The rationale for these selections and their applicability to the digital platform are summarized below.

**Table 4 tab4:** The eight selected digital markers and the number of recordings undertaken for each test activity during validation.

Activity	Subjects with PD	Control subjects
	Number of test recordings for each activity	
Voice vowel	315	183
Voice sentences	512	331
Resting tremor	211	154
Postural tremor	211	154
Alternate finger tapping	324	205
Pinch-to-size	294	205
Gait	280	202
Balance	284	201

PD, Parkinson’s disease.

##### Voice vowel and voice sentence tests

2.3.1.1

Difficulty in speech, known as dysarthria, is reported to be one of the earliest symptoms of PD, specifically involving degraded phonation, articulation, and prosody (123–126). Voice assessment is one of the most discriminatory features of PD and its changes may be the first motor sign in the prodromal phase (127, 128). To evaluate dysarthria, individuals typically undergo assessments that involve utilizing sustained-vowels, words, or sentences. Features extracted from voice data in the frequency domain include fundamental frequency, pitch, and harmonics, while features extracted in the time domain consist of amplitude, period, jitter, and shimmer. Singh and Xu (92) implemented several machine learning classification approaches on voice samples of individuals saying “Aaah” for 10 s from mPOWER dataset to differentiate between PD and non-PD cases. The authors reported a classification AUC of 0.99 when using L1-based feature selection in conjunction with SVM. Similarly, Despotovic et al. (91) achieved a classification accuracy of 96.92% by applying the gaussian processes Automatic Relevance Determination (ARD) to identify individuals with PD using sustained vowels from the Parkinson’s Telemonitoring dataset. Several studies have reported that features extracted from sustained vowels recordings are more effective in discriminating between PD and non-PD cases than features extracted from words or sentences (91, 129, 130). However, several studies have reported that using sentences is more effective than using sustained vowels for classification, with accuracy ranging from 82% to 99%, as sentences provide more insights into prosody, phonation, articulation (123, 131, 132).

While motor tests such as tremor, gait and finger tapping are applicable regardless of the individual’s language, in the case of speech tests, the subject may be unable to understand the test or complete it successfully due to challenges with pronunciation, which may influence the test results and their interpretation (133). To overcome this, the voice tests used for Parkinson’s disease risk survey digital platform implemented in Thailand comprise newly developed speech tests that use sustained vowels (making a loud “Aah” sound for 10 s to assess phonation) and speaking sentences in Thai language (to assess prosody and articulation), thereby enhancing its relevance for Thai native speakers.

##### Resting and postural tremor tests

2.3.1.2

Tremor is an involuntary, and often rhythmic, shaking of various parts of the body with one of the most common sites in subjects with PD being the hands. The types of tremors commonly used to test for a PD diagnosis are “rest” and “postural” tremor. A rest tremor involves placing the hands in a relaxed position, e.g., resting hands in the lap, with no intention of movement (134). Postural tremor describes tremor that occurs while maintaining a posture (135). Data obtained from a smartphone’s inertial sensors can be used to quantify the level of tremor (93), thereby helping to determine whether the person has PD. Features from tremor data are extracted in both the time and frequency domains. In the time domain, these features include temporal fluctuation, root mean square (RMS) of linear acceleration, and approximate entropy. In the frequency domain, they encompass power frequency and power spectral density. Surangsrirat et al. (94) reported 100% classification accuracy, sensitivity, and specificity using SVM as a classifier, tested with 10-fold cross-validation, and utilizing only the temporal fluctuation feature for classification.

##### Alternate finger tapping and “pinch-to-size” test

2.3.1.3

Impaired dexterity has been documented as one of the earliest motor signs in PD and can be demonstrated about 6 years prior to the diagnosis of PD (46). Abnormal dexterous movements can be detected by alternating two fingers tapping on the computer keyboard or on the smartphone (96, 136, 137). Studies have shown that the machine learning approach using the various parameters of finger tapping tests can discriminate PD from controls with good accuracy, suggesting that the alternating finger tapping test would be a promising digital marker to quantify subtle motor symptoms in early PD (96).

A finger pinching test, referred to in this study as the “pinch-to-size test,” will also be used to supplement the finger tapping test. This test was designed to detect PD tremor in fingers and hands by collecting screen touching data while subjects pinch their thumb and index finger to track the size of a circle on a mobile phone screen. The pinch-to-size test is similar to the finger tapping test, where subjects are asked to tap their index finger on the same hand repeatedly as fast as possible and move the index finger away from the thumb as far as possible after tapping (138, 139). This finger tapping test is normally used to assess the finger rigidity. The pinch-to-size test selected for the Parkinson’s disease risk survey assesses finer movement as well as the hand-eye coordination of both fingers because the pinching speed and size are constrained by the target circle’s shape. The pinch-to-size test is also convenient to perform, as it resembles the pinching movement used on a mobile phone screen to zoom in or out.

##### Gait and balance tests

2.3.1.4

People with PD can experience gait and balance disturbances, which may appear as slow walking, shuffling, dragging steps, and struggling to start or stop walking (140, 141). If combined with an unstable posture, the individual will be more susceptible to the risk of falling. The accelerometer and gyroscope functions of a smartphone can be used to quantify gait patterns. Features extracted from gait data are acceleration amplitude, gait speed, stride intervals, peak frequency, and wavelet bands. Pittman et al. (89) attained an accuracy of 92% in classifying PD and non-PD individuals using a decision tree and artificial NN using data collected during a walking activity (10 s walking and 10 s standing still). Similarly, Zhang et al. (90) employed deep neural network as the classifier, with the authors reporting an area under the receiver operating characteristic curve (AUC) of 0.87.

#### Digital marker validation and data analysis

2.3.2

The eight selected markers have been developed into a digital application that has been validated as described below. Validation was undertaken in a cohort of 343 people with PD (48.6% male) and 230 control subjects (27.9% were male) without PD. Participants undertook each test activity using a mobile application and data were recorded using the built-in sensors of the mobile phone, namely the accelerometer, gyroscope, microphone, and touch screen. The validation study was approved by the Human Ethics Committee of the Faculty of Medicine, Chulalongkorn University (IRB number 0804/65). All subjects gave written informed consent before the enrolment into the study, in accordance with the declaration of Helsinki. Performance on the eight test activities were recorded by each participant using a mobile application and the built-in sensors of a smartphone, namely the accelerometer, gyroscope, microphone, and touch screen. Details of how each testing activity was performed is described in Table 5.

**Table 5 tab5:** Performance methods for each of the digital marker test activities.

Marker	Description of test
Voice vowel	Participants pronounce the sustained vowel /a/, as in “*bar*,” for 10 s without holding their breath. The test is repeated three times for each participant.
Voice sentences	Participants read sentences aloud in the Thai language, such as the example sentence “*rod tid mak loey*,” which means “*The traffic is really jammed*.” The test includes a total of 25 sentences that are commonly encountered in real-life situations.
Resting tremor	Participants are instructed to place the mobile phone on one palm with the screen facing up and lay their hand in their lap. They are then asked to specify whether the device is on the left- or right-hand side by pressing on the screen. Finally, participants are instructed to keep their hand still, along with the device, for 20 s.
Postural tremor	Participants are instructed to hold the device and press on the screen to verify which side of the hand they are holding, then stretch out their arm and maintain that posture for 20 s.
Alternate finger tapping	Participants place the device on a flat surface. They are then instructed to use their index and middle fingers of one hand to tap on two circles that appear on the screen, alternating between the two fingers as quickly as possible while maintaining correct finger alternation within 10 s.
Pinch-to-size	Participants place the device on a flat surface. They are instructed to use their thumb and index finger of one hand to pinch, following the varying size of a circle that also moved randomly across the screen. The test is repeated five times for each participant.
Gait	Participants hold the device and walk in a straight line for 3 meters, then turn around and walk back to the starting position. The route for testing is set up to indicate the walking direction and the turning point.
Balance	Participants are instructed to put the device in a pocket after pressing start to begin the test. They then stand still for 30 s. A tone is played to signify the end of the test.

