#### Validation

2.2.3

There are various different approaches that can be used for the assessment of content validity; however, a review of the published literature suggests that there is no agreed consensus on the best method for patient-focused instruments (121, 122). Some studies use Expert Panel opinion only without any grading while others propose 3-, 4-, or 5-item grading systems. In our study, the content validity of the symptom questionnaire was initially evaluated by the Expert Panel for both its relevance to the clinical presentation of prodromal and early PD, and its applicability to the Thai population. We also used a standard 3-level anchor system in rating the questionnaire, as used successfully in other PD questionnaire studies (114). Each item was graded in three levels (0 = not relevant, 0.5 = moderately relevant, 1 = very relevant) (114). The content validity was calculated as the mean score of all items with any mean score > 0.5 being considered acceptable. Using our chosen method, the content validity for the questionnaire was a mean ± standard deviation (SD) of 0.97 ± 0.07 (range: 0.85–1.0).

The reliability of the questionnaire was tested on a cohort of 15 people with PD (7 male, 8 female; mean [± SD] age: 67.6 ± 9.7) and 15 control subjects (7 male, 8 female; mean [± SD] age: 51.8 ± 9.0) without PD using Cronbach’s alpha coefficient of the total score. A Cronbach’s alpha coefficient > 0.7 was considered as indicating good reliability. The Cronbach’s alpha coefficient for the questionnaire was calculated to be 0.939. Test–retest reliability was evaluated in a cohort of 100 people with PD (54 male, 46 female) with 3 months between the first and second tests. Demographic characteristics of the test–retest study participants are summarized in Table 3. Significant test–retest reliability was confirmed for all 20 questions (*p* < 0.001 in each case). Pearson’s correlation between PD and the total sum score of the 20-item questionnaire was R = 0.931 (*p* < 0.001). The Pearson’s correlation for each individual item is shown in Supplementary material 2. The receiver operating characteristic (ROC) curve for PD classification using the symptoms questionnaire with 10-fold cross validation which showed a mean area under the curve (AUC) of 0.92 ± 0.02.

**Table 3 tab3:** Demographic characteristics of subjects who participated in the questionnaire test–retest validation.

Parameters	Male (*n* = 54)	Female (*n* = 46)	*p*-value (Chi-squared test)

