##### Feature extraction

2.3.2.1

Features were extracted using Python SciPy library (142). SciPy.stats was used for statistical parameters (e.g., mean, SD, kurtosis, and skew). SciPy.signal and SciPy.fft were used for extracting time (e.g., period amplitude) and frequency domain features (e.g., harmonics and formants). The extracted features were labeled according to the participant’s group before feeding to the machine learning classifier.

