##### Choice of machine learning classifier

2.3.2.2

Many studies have demonstrated the effectiveness of using machine learning classification algorithms to accurately differentiate individuals with and without PD based on data collected through smartphone applications.

Initially, the performance of three machine learning classifiers was compared: multilayer perceptron (MLP), SVC, and random forest (RF) using the hold-out method for dataset splitting, to find which would be best suited for the Parkinson’s disease risk survey data. We used the default settings for each classifier from scikit-learn (143) version 1.3.0. The RF algorithm was chosen because it demonstrated higher accuracy in classifying PD compared to SVC and performed comparably to MLP in our preliminary analysis using tremor and gait recordings. The superior performance of the RF algorithm compared to SVC and MLP aligns with the findings of Sarkar et al. (144).

RF is a machine learning algorithm composed of an ensemble of decision trees. In a classification task, each branch of the decision tree is trained using subsets of sampled training data labeled by the predicting classes. During the learning process, decision trees perform a series of comparisons on selected input features (node splitting) until a predicting class is assigned to the feature. The final predicted class of the RF is determined by the majority of the output classes from the decision trees.

In the validation study, an RF classifier was used to predict whether activity recordings were from a person with or without PD. The forest consisted of 100 trees, and Gini impurity was used to measure the quality of splits. The maximum number of features was determined by the square root of the total number of features before searching for the best node splitting. Ten-fold cross-validation was employed to assess the generalizability of the classifiers. In each test activity, the data was divided into 90% for training and 10% for testing sets. Classifiers trained specifically for a type of activity are referred to as specialized classifiers.

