##### Validation results

2.3.2.5

Table 6 summarizes PD classification performance using classifiers specialized for individual activity data, measured by the mean AUC with 10-fold cross validation. PD classification using balance data achieved the highest mean (±SD) AUC of 0.88 ± 0.06. The use of voice vowels resulted in a mean (±SD) AUC of 0.82 ± 0.04, which was the lowest value.

**Table 6 tab6:** Mean area under the receiver operating characteristic curve after 10-fold cross validation for each test activity.

Activity	Mean AUC ± SD
Balance	0.88 ± 0.06
Postural tremor	0.87 ± 0.06
Dual tapping	0.86 ± 0.05
Pinch-to-size	0.85 ± 0.05
Gait	0.84 ± 0.07
Questionnaire	0.83 ± 0.04
Voice sentences	0.83 ± 0.04
Rest tremor	0.83 ± 0.06
Voice vowel	0.82 ± 0.04

Test activities are sorted by their mean area under the curve (AUC) in descending order.SD, standard deviation.

Using voice vowel and voice sentence data ROC curves for PD classification using RF with 10-fold cross validation showed mean (±SD) AUC values of 0.82 ± 0.04 and 0.83 ± 0.04, respectively (Figure 6). Using resting tremor data and postural tremor data, ROC curves for PD classification using RF with 10-fold cross validation showed mean (±SD) AUC values of 0.83 ± 0.06 and 0.87 ± 0.06, respectively (Figure 7). Using dual tapping and pinch-to-size data, ROC curves for PD classification using RF with 10-fold cross validation showed mean (±SD) AUC values of 0.86 ± 0.05 and 0.85 ± 0.05, respectively (Figure 8). Using gait and balance data, ROC curves for PD classification using RF with 10-fold cross validation showed mean (±SD) AUC values of 0.84 ± 0.07 and 0.88 ± 0.06, respectively (Figure 9).

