**Figure 9 fig9:**
[figure not shown]
Receiver operating characteristic of classifiers using gait data (left) and balance data (right).

Overall, the AUC values of the specialized classifiers ranged from 0.82 to 0.88. Balance testing achieved the highest AUC of 0.88. The ensemble classifier, which utilized a combination of questionnaire responses, voice vowels, rest tremor, gait and balance activities achieved a PD prediction accuracy of 0.9108 (Table 7). Taken together, these results confirmed the validity of the selected digital markers and the mobile application and testing system for distinguishing between subjects with and without PD.

**Table 7 tab7:** The top eight test activity combination sets achieved the highest mean accuracies when evaluated on five randomly sampled test sets.

Activity count	Activities									Accuracy of 10-fold CV test set randomly selected 5 times	
	Questionnaire	Voice sentence	Voice vowel	Postural tremor	Rest tremor	Gait	Balance	Dual tap	Pinch-to-size	Mean	SD
5	✓		✓		✓	✓	✓			0.9108	0.012357
8	✓	✓	✓	✓	✓	✓	✓		✓	0.9106	0.006148
8	✓	✓	✓	✓		✓	✓	✓	✓	0.9094	0.011908
5	✓	✓	✓	✓			✓			0.9094	0.006285
8	✓		✓	✓	✓	✓	✓	✓	✓	0.9046	0.010918
7	✓		✓	✓	✓	✓	✓		✓	0.9042	0.009391
8	✓	✓		✓	✓	✓	✓	✓	✓	0.9032	0.013221
7	✓		✓	✓		✓	✓	✓	✓	0.9018	0.008849

Activity count indicates the number of specialized classifiers used for ensemble learning.CV, cross validation; SD, standard deviation.

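### In the digital-marker validation cohort, PD and control groups differ markedly in sex and age by group is not reported, so the AUCs may contain an unquantified demographic contribution

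*Protocol article*

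**What the plan says.** Section 2.3.2 of the protocol article describes the cohort on which the eight digital markers were validated: "Validation was undertaken in a cohort of 343 people with PD (48.6% male) and 230 control subjects (27.9% were male) without PD". It gives no age for either group.

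Section 2.3.2.1 says: "The extracted features were labeled according to the participant’s group before feeding to the machine learning classifier". Section 2.3.2.2 then trains a random forest for each activity and adds: "Ten-fold cross-validation was employed to assess the generalizability of the classifiers". Sections 2.3.2 to 2.3.2.5 mention no matching, weighting or stratification on age or sex, and no benchmark model using only those two variables. Section 2.3.2.4 does examine imbalance in the numbers of PD and non-PD recordings, by a precision-recall curve for the voice tests. It does not examine imbalance in participant characteristics between the classes.

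Section 2.3.2.5 reports single-activity AUCs from 0.82 (voice vowel) upwards: "PD classification using balance data achieved the highest mean (±SD) AUC of 0.88 ± 0.06". The best ensemble has an accuracy of 0.9108 (Table 7). The article concludes that "these results confirmed the validity of the selected digital markers", and the last paragraph of the Discussion presents the platform as validated and highly accurate for screening the Thai population.

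The only ages given for PD and control participants side by side come from a separate sample, the questionnaire reliability cohort in section 2.2.3. Its 15 PD participants averaged 67.6 years (SD 9.7). The comparison group there is given as "15 control subjects (7 male, 8 female; mean [± SD] age: 51.8 ± 9.0) without PD".

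**The concern.** A classifier trained to separate two groups will use any feature that differs between them, whether the disease or something else causes the difference. Some of the inputs can carry demographic information. Section 2.3.1.1 notes in its rationale that "Features extracted from voice data in the frequency domain include fundamental frequency, pitch, and harmonics", and pitch differs between men and women. Gait speed and stride intervals (section 2.3.1.4), sway and tapping speed can vary with age. With 20.7 percentage points more men among the PD participants, and age unknown, some of the apparent discrimination could be recognition of sex or age.

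Ten-fold cross-validation draws its training and test folds from the same imbalanced cohort. A demographic shortcut learned in training therefore works equally well in testing, so the procedure guards against overfitting but not against this.

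At stake is what the AUCs can support. The tool is meant for all citizens above 40 (section 2.1), among whom age and sex vary widely. If the classifiers do use such signal, error rates in that population could differ by sex and age, and pooled true positive and true negative rates would hide it.

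**Working it through.** **1. Sex imbalance.** Inputs from section 2.3.2: 48.6% of 343 and 27.9% of 230.
- Nearest whole counts: 343 × 0.486 = 166.7, so 167; 230 × 0.279 = 64.2, so 64. These return 48.7% and 27.8%, each 0.1 point from the printed figure, which is trivial.
- Odds ratio = (167 × 166)/(64 × 176) = 2.46.
- Difference from these counts = 20.9 points (95% CI 13.0 to 28.7). Pearson chi-square = 24.9, p = 6e-7. Other neighbouring whole counts give p no larger than 1.5e-6 (2.2e-6 with continuity correction).

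**2. What sex alone could achieve.** For a binary marker, AUC = 0.5 + (p1 − p2)/2 = 0.5 + (0.486 − 0.279)/2 = 0.60. This is well below 0.82.

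**3. What age alone could achieve.** Under normality, AUC = Φ(gap / √(SD1² + SD2²)). The gap in the 343/230 cohort is not reported, so any value is an assumption. The article offers two indirect indications.
- *Reliability cohort (15 + 15, section 2.2.3).* Gap = 67.6 − 51.8 = 15.8 years. Standard error = √(9.7²/15 + 9.0²/15) = 3.42, so the 95% CI is about 8.8 to 22.8. AUC = Φ(15.8/√(9.7² + 9.0²)) = Φ(15.8/13.23) = 0.88.
- *Retest cohort (100 people with PD, Table 3).* Mean age = (54 × 62.0 + 46 × 56.1)/100 = 59.3. Variance = within-sex (54 × 14.8² + 46 × 10.2²)/100 = 166.1, plus between-sex 0.54 × 0.46 × 5.9² = 8.6, total 174.8 (SD 13.2). Against the same 15 controls, gap = 59.3 − 51.8 = 7.5 years and AUC = Φ(7.5/√(174.8 + 81.0)) = Φ(0.47) = 0.68.

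**4. Age and sex together, over a range of assumed gaps.** Common SD √((9.7² + 9.0²)/2) = 9.36. The score is the log-likelihood ratio of age and sex, with the sex split of the validation cohort. The combined AUC was simulated with 400,000 per group.

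| Assumed age gap (years) | AUC, age alone | AUC, age + sex |
|---|---|---|
| 0 | 0.50 | 0.60 |
| 3 | 0.59 | 0.65 |
| 5 | 0.65 | 0.69 |
| 8 | 0.73 | 0.75 |
| 10 | 0.78 | 0.79 |
| 15.8 | 0.88 | 0.89 |

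The retest-cohort figure of 0.68 lies below the 8-year row mainly because that PD cohort has a larger SD (13.2).

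**5. Gap needed to match the markers by age alone.** Gap = Φ⁻¹(AUC) × 9.36 × √2, which gives 12.1 years for 0.82 and 15.6 years for 0.88.

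These figures suppose that age and sex are known exactly. Sensor features recover them imperfectly, so the AUCs are ceilings on what demographics alone could contribute. No corrected AUC can be calculated from the article.

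**The case against.** A reader might infer that AUCs of 0.82 to 0.88 largely reflect demographics. The document does not support that. Sex is the only measured imbalance, and it yields 0.60. The 15.8-year age gap belongs to a different, small sample that was sex-balanced (7 men and 8 women in each group), so its make-up clearly differs from that of the digital cohort. The larger PD sample points to a gap of about half that size, and a gap of zero cannot be excluded. Nor does the ranking of markers favour a pitch-driven explanation: voice vowel has the lowest AUC and voice sentences are near the bottom, while balance and postural tremor lead. The sentence on pitch is literature rationale, not a list of the features actually extracted.

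It is also tempting to say that older men without PD will be over-flagged and younger women with PD missed. The article has no data on this, and the direction for age depends entirely on the unreported gap. Referral to a neurologist for confirmation, and the acknowledged need for further model training to avoid overdiagnosis, limit the harm from false positives. They do not correct a biased AUC or recover missed cases.

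Finally, this is a condensed article, so it cannot be said that no adjusted analysis is planned anywhere. Only its absence from what is reported here is established.

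These objections limit the size of the claim. They do not remove the point. The validation is a completed analysis, interpreted in the article as confirming validity; the imbalance is large, and the limitations discussed there do not mention it.

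**Conclusion.** The concern holds in a limited form. The sex difference between cases and controls is documented and far beyond chance, age by group is missing, and no reported analysis separates PD signal from demographic signal. The AUCs and the accuracy may therefore contain a demographic contribution of unknown size.

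Sex cannot account for the results by itself. Whether age adds a little or a lot depends on a gap that the article does not report: under the assumptions shown, the ceiling for age and sex together runs from 0.60 with no gap to 0.89 at 15.8 years. Different error rates by sex and age in the field are a conditional possibility, not a finding. What the article cannot yet support is the unqualified statement that validity has been confirmed.

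**What to change.** Re-analyse the existing validation data; no new participants are needed.

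1. Report age by group for the 343 and 230 participants.
2. Report the AUC of a model using only age and sex, under the same cross-validation, and the paired gain over it for each marker and for the ensemble.
3. Report AUC with age and sex balanced between PD and controls, by weighting or on a matched subset, and AUC, TPR and TNR within sex and age bands.
4. Make the validity statement in section 2.3.2.5 and the claim in the last paragraph of the Discussion conditional on those results. Until they are available, name the imbalance among the limitations.

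Section 2.2.1 says that the survey was designed to capture basic demographic data, but this does not prove that age was recorded for the validation cohort. If it was not, do the sex-based analyses and state the limitation.

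The cost is analyst time, a smaller effective sample, wider intervals and probably lower AUCs.
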